### Who will take informed consent?

A trained research officer will contact potential participants/parents and undertake the informed consent process. This person will use culturally secure patient information documents that have undergone a rigorous development process that included feedback from stakeholders and 18 Western Australian First Nations community members from regional, remote and metropolitan areas.

### Additional consent provisions for collection and use of participant data and biological specimens

Confidentiality of enrolled participants will be ensured through use of a unique identifier code for all collected, shared, and maintained data to protect confidentiality before, during, and after the study. De-identified data for analysis will be stored in REDCap software (secured, passcode protected and encrypted research database).

Participants can withdraw consent at any time and do not need to provide a reason. If a participant wishes to withdraw from the study, the process for withdrawal is outlined on the consent form. Once withdrawal of consent has been obtained, no further data will be collected. Participants will be informed that their clinical care will not be affected if they choose to withdraw at any time.

### Interventions

#### Explanation for the choice of comparators

Each site will have three groups of participants, (i) Nil intervention control group, (ii) Health information only control group, and post-intervention group.

#### Intervention description

The medical follow-up strategy (henceforth termed ‘strategy’) was informed by our previous research [13, 14] and methodological approaches [15], and is consistent with Australian [16] and International [17] guidelines for children at high risk of developing bronchiectasis. Implementation of the strategy core components will be adapted to the unique context of each study site; the core components are outlined in Table 1.

**Table 1 Tab1:** Core components of medical follow-up strategy

Core components of the medical follow-up strategy	How each component will be provided?	Who will be involved in providing/delivering the core component?	Outputs	Outcomes (How we will know the core component was delivered as intended)
1. First Nations lead	• Advisory lead on all cultural components of project	• First Nations lead	• Culturally secure operations with First Nations knowledge privileged	• First Nations lead identified and appointed and employed for duration of study
2. Stakeholder engagement	• Engagement occurs with focus groups and interviews for the purpose of identifying current state, barriers and facilitators to providing the strategy • Inner setting: patients, HCPs, executive • Outer setting: primary care HCPs and other key stakeholders such as umbrella First Nations primary care organisation) and the Telethon Kids BREATH team consumer reference group	• Qualitative experts will lead the interviews, focus groups and analysis • Interviews and focus groups will capture voice of parents, HCPs and primary care HCPs involved with children hospitalised with ALRIs	• Identified barriers and facilitators	• Written report summarizing key findings, process map and tailored implementation of strategy for each site
3. Training of clinicians and other health staff	• Online module and podcast(s) accessible and free of charge • In-person training	• Clinical champion will promote module and podcast at each site • In-person clinical training by pediatric respiratory clinician • Cultural training by Aboriginal cultural educator	• Module and podcast hosted on National website • Clinical/cultural training accomplished	• Metrics of completions at each site (electronic capture system) • Percentage or proportion of HCPs trained out of the total number (denominator) who could be trained at each site
4. Educational resources	1. Health information flip chart 2. Health facts sheet for parents 3. Letter to local clinic	• Champion at each site ensures accessibility of documents	• Educational resources adapted for each site • Available on internet/intranet • Hard copies easily accessible in clinical workrooms	
5. Patient admission process	1. Patient is identified as being First Nations and local clinic is updated on electronic record system 2. Parent receives lung health education and is instructed to follow-up in 1-month at local clinic	1. Clerks 2. Doctors 3. Nurses	• Automated SMS sent to parent	• Audit of discharge summary to check First Nations identification and local clinic contact
6. SMS follow-up reminder	• A SMS is sent to each patient at 4-weeks post discharge with reminder to take child to local clinic for follow-up if chronic wet cough	• Site Information Technology (IT) department	• Automated SMS sent to each patient at 4-weeks post discharge	• Number of SMS reminders recorded
7. Discharge process	• Electronic discharge summary requires instructions for primary care clinicians • Instructions to be integrated into the existing electronic discharge form via template	• Doctor to complete discharge summary with all required information • IT technician at hospital site to embed template with instructions for easy integration by doctor when completing summary	• Instruction template is integrated into the electronic discharge summary system	• Audit of discharge summary compliance with required information (see Additional file 6)
8. Local champions	• Champion helps HCPs to uptake new processes and reminds HCPs about best practice at routine staff meetings	• Identified by clinical lead at each site	• Champion is provided with training at each site	• Number of champions and interactions recorded at each site

*HCP* healthcare provider, *IT* information technology, *SMS* short message service

### Criteria for discontinuing or modifying allocated interventions

The medical follow-up strategy was developed in a study at Perth Children’s Hospital [14]. Delivery of the strategy’s core components (Table 1) will be adapted to the workflows and structure of sites using a combined decolonising research approach [15], which includes Participatory Action Research (PAR) [14] and the Consolidated Framework for Implementation Research (CFIR). The CFIR provides a structure for identifying a range of factors that can facilitate or hinder the implementation of evidence-informed interventions. This implementation approach aims to maximize translation potential through the continuous process of action, reflection and feedback allowing adjustments to the project throughout all phases [18]. In this way, the implementation can be optimised to ensure the benefits of the strategy are sustainable over the long term, beyond the project, and that scale-up is feasible across other service provision sites. Implementation science informs our approach, alongside context sensitive adjustments of implementation processes that consider First Nations consumer views to ensure engagement, effectiveness, and sustainability. Identification of adaptations required for implementation of strategy core components will involve interviews and focus groups with stakeholders, including:Healthcare providers (HCP): Purposive sampling to recruit HCPs at hospital or local primary care clinic who are involved in caring for patients or providing follow-up following an admission for ALRI.Parents: Purposive sampling to recruit parents of First Nations children hospitalised with ALRI. A First Nations researcher will be available for all interviews with First Nations participants.
Inclusion criteria of participants for interviews:HCP: Any HCP within the hospital or local clinic who are involved in the medical care of First Nations children with ALRI, including but not limited to doctors (paediatricians, respiratory physicians, service coordinators, Aboriginal health practitioners, primary-care liaison personnel), nurses and clerks.Parents of First Nations children hospitalised with ALRI. Parents may include grandparents, foster parents or other family members within the kinship system, who are responsible for caring for the hospitalised child.External stakeholders: Relevant stakeholders such as the Aboriginal Community Controlled Health Councils at a state and local level, peak bodies, such as the Aboriginal Health Council of Western Australia.
The purpose of the interviews and focus groups is to ascertain barriers and facilitators to implementing the strategy and to understand the perspectives of parents and HCPs about the need for medical follow-up. Interviews and focus groups will be conducted by at least two interviewers: a content expert (clinician or Aboriginal lead) and a qualitative researcher. Interview participants will be recruited during the “health information only” period, prior to the implementation of the strategy.

Interviews and focus groups will be recorded by audio or with hand-written notes by two researchers (depending on interviewee preference). The interview guides (see Additional file 1, Additional file 2, Additional file 3) were developed by two researchers with experience in qualitative methods and a pediatric respiratory physician. The draft questions were tested with two families and two HCPs at Perth Children’s Hospital and then refined. Audio taped interviews will be transcribed verbatim and notes compared and checked with at least two qualitative research experts. Issues related to confidentiality, interview bias, role designation, power imbalance and assumptions influencing participants will be discussed and resolved within the research team. Interviewee transcript review will be undertaken when clarification is necessary and/or if the interviewee has indicated they would like to review their transcript.

Qualitative component sample size (interviews and focus groups)HCPs: ~ 8–10 focus groups with 6–8 participants and ~ 10 individual interviews per site.Parents: ~ 15–20 individual interviews per site.
Sample size for the qualitative component was estimated considering the concept of information power [19] and the impacting dimensions; study aim, sample specificity, use of established theory, anticipated quality of dialogue and the analysis strategy. Participants will be recruited to the parent and HCP groups respectively until thematic saturation is achieved for each group i.e., no new information or themes are evident.

#### Analysis of qualitative data (interviews and focus groups)

Reflexive thematic analysis, using deductive and inductive analysis [20] informed by Creswell and Creswell’s six-steps [21] will be undertaken to map themes by identifying codes and then sub-themes as agreed by the researchers using an iterative process. Implementation factors (CFIR) identified in the interviews will inform implementation processes (e.g., strategies for mitigating barriers) at each site. Trustworthiness will be achieved by ensuring the researchers address four key criteria outlined by Nowell et al. [22]. The Consolidated Criteria for Reporting Qualitative research [12] (COREQ) will be used to report focus groups and interview data.

### Strategies to improve adherence to interventions

Fidelity to the strategy at each site will be managed through tracking log of outputs and with field notes. Implementation process will be tracked with fieldnotes.

**Relevant concomitant care permitted or prohibited during the trial**

N/A

**Provisions for post-trial care**

N/A

### Outcomes

The study outcomes consist of three categories: (i) health, (ii) economics and (iii) implementation.

### Health outcome/primary outcome measure (Quality of Life (PC-QoL))

The primary outcome is the parent-proxy Cough-specific Quality of Life (PC-QoL) for children with chronic wet cough. Effective follow-up and management of children hospitalized with ALRIs will be assessed by measuring PC-QoL between 6 weeks and 3 months after hospitalization. We will use the 8-item version of the PC-QOL tool that has been shown to be a valid, reliable, and responsive tool for measuring the burden of chronic cough in children. This tool has been used effectively in First Nations settings [17, 18].

Rationale: children with ongoing respiratory symptoms and cough post hospitalization will have improved quality of life if they receive effective medical follow-up at one-month post discharge. The PC-QoL scores will be compared pre and post implementation in different children who had a chronic wet cough post-discharge. Children with chronic wet cough post-hospitalization who received timely follow-up and optimal management will have better cough specific QoL than children who did not. It has been determined, using the anchor method, that 0.9 is the calculated minimum important difference in PC-QOL [23].

Respiratory symptoms after ALRI should typically resolve within 4 weeks. Children with ongoing wet cough 4 weeks post-hospitalization are likely to have protracted bacterial bronchitis that should resolve if detected and managed in a timely way. Hence, if children receive appropriate follow-up and management a month after discharge then we expect their cough related QoL to be better after 6–12 weeks than those who did not (waiting 6–12 weeks allows time for management to be completed in those children with chronic wet cough who may require up to a month of antibiotic treatment).

The PC-QoL tool will be administered by a research officer in-person at the hospital sites, over the phone, or electronically (online option via REDCap for those participants who would prefer this option). Participants will be contacted by the research officer via text message or telephone.

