### Secondary outcome measures

Cultural competency of HCP while child hospitalized (parent report).Instructions for medical follow up given by clinician (parent report).Follow-up rates of children within 1-month (range 3–6 weeks) post hospitalization for ALRI (parent report).In children with chronic wet cough:Antibiotics prescribed at follow-up (parent report).Adherence to prescribed antibiotics (self-report).Cough resolution at 6–12 weeks post discharge (parent report).Discharge summary audit: An audit of the discharge summary to evaluate patient management (see Additional file 6):First Nations ethnicity recorded.Local clinic/doctor identified.Instructions given to parent to follow up in 1-month with local doctor.Instructions to the local clinic/GP clearly stipulates to check child for ongoing chronic wet cough, absence or presence of ongoing other signs and suggest appropriate management if chronic wet cough is present. Link to appropriate clinical practice guidelines for the management of chronic wet cough provided.*Note: an audit of discharge summaries will be conducted each month. De-identified results (audit and feedback) will be provided to the HCPs each month at their regular departmental meeting to facilitate service improvement as part of implementation process.*
Secondary outcome measures 1–4 will be captured by telephone follow-up at 6–12 weeks post discharge. To ensure culturally secure engagement, a standardized script will be used to provide context by the telephoning research officer. The research officer who telephones the parent will first introduce themself and identify from where they are calling. The officer will provide context for the call, i.e., remind parent about the study and child’s recruitment at recent hospital admission. The questions are outlined in question 2, 3, 5 of Additional file 7.

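### The PC-QoL window opens at 6 weeks, about 1 to 4.4 weeks before a full-month course begun at timely follow-up can end, so an unknown share of correctly managed children may be scored mid-treatment

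*Protocol article*

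**What the plan says.** All references are to the protocol article.

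- **Primary outcome section.** Effective follow-up is assessed by "measuring PC-QoL between 6 weeks and 3 months after hospitalization". The rationale places follow-up and management a month after discharge. It then states that "waiting 6–12 weeks allows time for management to be completed in those children with chronic wet cough who may require up to a month" of antibiotics.
- **Secondary outcome measures.** Timely follow-up is defined as "Follow-up rates of children within 1-month (range 3–6 weeks) post hospitalization for ALRI (parent report"). Antibiotic adherence and cough resolution are collected by telephone at 6–12 weeks.
- **Table 1, component 6.** "A SMS is sent to each patient at 4-weeks post discharge with reminder to take child to local clinic".
- **Economic analysis.** A child with chronic wet cough who was properly managed and whose cough resolved is counted as a bronchiectasis case prevented.

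The article gives no target day within the window, no distribution of course lengths, and no rule tying the call to the end of treatment.

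**The concern.** The window rests on a stated property: management is complete by the time PC-QoL is taken. If management starts about a month after discharge and can last a month, it ends at about two months, yet scoring is allowed from six weeks. A child seen in week 6 counts as followed up on time and could be scored that same week.

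The children affected are those managed as the strategy intends. For them the primary outcome would record an unfinished course, and adherence and cough resolution, asked at 6–12 weeks, would have the same problem. A cough still present mid-course would also not count as a case prevented in the economic evaluation. The expected direction is toward a smaller post-intervention effect, and the result would depend partly on when the research officer happened to reach the parent.

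**Working it through.** **1. When does a full-month course end?**
Inputs: follow-up at weeks 3–6 (Secondary outcome measures); SMS at week 4 (Table 1); treatment of at most a month (primary outcome section). A month is taken as 4.0 to 4.35 weeks.

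End of course = follow-up week + course length.

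| Follow-up | End of course (weeks) | After week 6 by |
|---|---|---|
| Week 3 | 7.0–7.35 | 1.0–1.35 |
| Week 4 (SMS) | 8.0–8.35 | 2.0–2.35 |
| One calendar month (4.34) | 8.3–8.7 | 2.3–2.7 |
| Week 6 | 10.0–10.35 | 4.0–4.35 |

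So the stated property fails at the lower limit for every full-month course begun at week 3 or later. It holds at the upper limit (12 weeks, or about 13 if three months) in every row. A 2-week course begun at week 4 ends at week 6, so shorter courses can fit.

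**2. What share could be scored mid-treatment?**
The documents give no dates, so this is a range under assumptions. Let the call be uniform on weeks 6 to e (e = 12 or 13), the visit F uniform on weeks 3–6 or 4–6, and the course length L. Then

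P(call before end of course) = E[max(0, F + L − 6)] / (e − 6).

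- L = 4, F on 3–6: (4.5 + 4 − 6)/6 = 0.417; divided by 7, 0.357.
- L = 4, F on 4–6: (5 + 4 − 6)/6 = 0.50; divided by 7, 0.429.
- L = 4.35, F on 4–6, e = 12: (5 + 4.35 − 6)/6 = 0.558.
- L = 3: 1.5/7 = 0.214 up to 2/6 = 0.333.
- L = 2, F on 3–6: E[max(0, F − 4)] = (2²/2)/3 = 0.667, giving 0.111 (e = 12) or 0.095 (e = 13).
- L = 2, F on 4–6: 1/6 = 0.167 or 1/7 = 0.143.

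This gives 36–56% if every course lasts a full month, 21–33% for 3-week courses and 10–17% for 2-week courses. If calls cluster in weeks 6–8, with visits over weeks 3–6, the share is 92–96% for full-month courses and 33% for 2-week courses. If all calls fall after about week 10.4 it is zero.

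**3. What could dilution do to the primary contrast?**
Inputs from Sample size: nil-intervention 2.7, post-intervention 4.3, SD 1.3, 12 per period, two-sided alpha 0.05.

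The plan's figure reproduces: noncentrality 1.6/(1.3 × √(2/12)) = 3.01, critical t on 22 df = 2.07, power 82%, against the stated >80%.

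Now assume that 42% are scored early and show half the benefit. The difference is 1.6 × (1 − 0.42 × 0.5) = 1.26 and the noncentrality is 1.26/(1.3 × √(2/12)) = 2.38, so power is about 62%. At the planned 20 per stage (Pragmatic data collection), with the same t-test and no clustering, power goes from about 97% to about 85%. The half-benefit figure is an assumption and is not in the documents.

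**4. Would a later target remove the problem?**
With calls uniform on weeks 10–13 and visits on weeks 3–6, the share is 0 for L = 4. For L = 4.35 it is E[max(0, F − 5.65)]/3 = (0.35²/2)/3/3 ≈ 0.007, or under 1%.

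**5. When is the nil-intervention group called?**
These children were hospitalised 6 weeks to 6 months before trial start (Eligibility criteria) and are telephoned only after a 3-week opt-out period (Recruitment). If letters go out at trial start, calls begin at about 6 + 3 = 9 weeks and run to about 26 + 3 = 29 weeks. Comparison children may therefore be scored later than post-intervention children.

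**The case against.** A reader might infer that many treated children will be scored mid-treatment. The documents do not support that. A month is given as a maximum for some children, there are no data on course lengths, visit dates or call dates, and the possible share runs from zero to over 90%. The 36–56% range gives every child the maximum course. Call scheduling within the window is also detail that an article may leave to the full protocol. This part of the objection stands.

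A reader might also infer that the window never allows management to finish. It does, from about week 10.4 onward.

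Nor should the effect be sized by shrinking the 0.7 step from the pre-implementation mean (3.6) to the post-implementation mean (4.3). The primary contrast is nil-intervention against post-intervention, planned at 1.6. On that contrast the illustrative 1.26 is still above the 0.9 minimum important difference. The 4.3 comes from the team's earlier data at unstated times after discharge, so some dilution may already be in it. The bias as described would not create a false benefit.

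Finally, a strict 10–12 week window in every stage would be costly. Nil-intervention calls may run to about 29 weeks, and with about 20 children per stage in remote settings, lost contacts matter. That rules out a rigid window but not a later target in the prospective stages. None of these points rescues the stated rationale at its early end.

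**Conclusion.** The point holds in limited form. The claim that the wait lets management finish conflicts with the article's own times: for full-month courses begun at weeks 3–6, the window opens about 1 to 4.4 weeks too early. An unknown share of correctly managed children may therefore have PC-QoL, adherence and cough resolution recorded during treatment. Under uniform timing that share is about 10–17% with 2-week courses and 36–56% with full-month courses.

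Dilution of the post-intervention result is likely, but its size cannot be derived from the documents. The fall from 1.6 to about 1.26, and from 82% to 62% power at 12 per period, rests on assuming that 42% are scored early with half the benefit. This should be fixed. It does not invalidate the design, and the article's power figures are not in question.

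**What to change.** 1. Reconcile the primary outcome section, the Secondary outcome measures and Table 1 on window, follow-up range and treatment length, and correct the sentence on completed management. No treatment rule is proposed here; only the time of measurement changes.
2. In the two prospective stages, schedule the primary PC-QoL and the cough-resolution and adherence items in the later part of the existing window: target about week 10 up to the stated 3 months. Align the secondary items' 12-week limit with that.
3. Keep assessments made earlier in the window. Record weeks since discharge and whether treatment is ongoing, and use both in a sensitivity analysis. Ongoing treatment is itself a consequence of the strategy, so it should not be a covariate in the primary model.
4. For the nil-intervention group, record time since discharge and account for it in the comparison instead of imposing a 10–12 week window.

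The cost is protocol wording, call scheduling and two recorded items. A later target may lose some contacts, which matters with about 20 children per stage, and parents must recall the ward stay over a longer interval. The Trial status section says recruitment has not commenced, so the change can be made before any call; calls already made early could not be re-timed.
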